#### Information delivery and post-information delivery questionnaires

We will randomly assign patients in a 1:1 ratio into information delivery mode Arm 1 or Arm 2. As noted previously, the two arms will be stratified within language (English or Spanish) and health literacy level [22] (lower vs. higher) (*n* = 150/stratum). We will use block randomization techniques to ensure that there are equal numbers in each arm per study site and stratum using a centralized, random assignment computerized system. Randomization sequences by language and health literacy level will be posted on a secure website that RAs across all four sites will consult when assigning participants to study arms. The advantage of this approach is that we can monitor enrollment and balance within study arms and across study sites easily, address concerns as they arise, and permit efficient use of study resources. The two groups will differ by the following:Arm (1): HIV/AIDS and HIV testing video: Participants in Arm 1 will watch the video, “What do you know about HIV and HIV testing?” (in English or Spanish) on a tablet computer in the ED while the RA waits. They will listen to the audio components using disposable headphones.Arm (2): HIV/AIDS and HIV testing pictorial brochure: Participants in Arm 2 will be provided with a copy of our HIV/AIDS and HIV testing pictorial brochure (in English or Spanish) to review in the ED. Arm 2 participants will read the brochure while the RA waits. The RAs will not provide clarifications or assistance with the information in the pictorial brochure.

After watching the video or reviewing the pictorial brochure, all patients will complete the post-information questionnaires using the automated telephone key-pad response system (the HIV risk self-perception and value of HIV testing, HIV/AIDS and HIV testing information delivery mode preferences and satisfaction, the HIV/AIDS and HIV testing knowledge, and the HIV risk-taking questionnaires). Patients will receive a re-chargeable gift card for participating.

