#### Sample size considerations

The study sample size is *n* = 1200, with equal size strata (*n* = 150) by language, health literacy level, and information delivery mode (Fig. 4). This sample size is based on a 2x2x2 full factorial design and will satisfy the requirements for analysis of the two primary aims and the four alternative hypotheses paired with each aim. The minimum sample size is calculated for a power of 0.80 and a two-sided *α = 0.05* level of significance (Table 3). In general, a larger sample size is needed for greater variation of scores within study arms and strata, lower within-person correlations of scores, and higher loss-to-follow-up. To maximize power, we chose conservative values based upon our prior studies. We increased the sample size by 20% to account for the heterogeneity in patients among the four study sites, and by a conservative additional 25% to account for possible attrition. Based upon other 12-month ED intervention follow-up studies [10], HIV/STD testing studies [57–59], and studies conducted at our own ED [60, 61], a 25% attrition rate at 12 months likely is a worst-case scenario. We expect that our experience and enhanced measures to encourage and facilitate follow-up will result in higher follow-up rates. As of publication of this manuscript, 1165 participants enrolled completed the three-month follow-up.

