**Fig. 4 Fig4:**

Sample size by study arm, language, and health literacy level

**Table 3 Tab3:** Sample size rationale by primary aims

Primary Aims	Minimum sample by stratum	Total minimum sample	Rationale and assumptions for minimum sample sizes and final sample sizes for each primary aim
Aim 1. Short-term improvement in HIV/AIDS and HIV testing knowledge ** HA1**: 3-way interaction (mode*language*literacy level) ** HA2**: 2-way interaction (mode*language or literacy level) ** HA3**: no interaction (difference by mode only) ** HA4**: no difference	**125** This **minimum** sample size by stratum will yield a power of 0.80, 0.97 and 0.99 for testing HA1, HA2, HA3 versus HA4 (HA4 as the NULL) Final sample per stratum (information delivery mode, language, and health literacy level) is 150	**1000** The **final sample** after adding 20% to account for the heterogeneity in patients among study sites is **1200** = 1000*(1 + 20%)	• Based on our prior video studies [17, 19, 21], we assume that the scores on the 25-item questionnaire is a normal distribution with a standard deviation of ~ 3 • Before information delivery, mean scores of the two arms are assumed to be the same (due to random assignment) per stratum • Short-term within-person correlation is 0.7 or higher [21] • The pictorial brochure will improve knowledge by an average of 2 points. The video will improve the knowledge by an average of 3.5 points. The effect size is Δ = 3.5–2 = 1.5. (HA3) • 2-way intrxn (mode*language or literacy level) effect size is Δ = 1.5 + 0.75 = 2.25. (HA2), e.g. for those speaking English OR with high health literacy • 3-way intrxn (mode*language*literacy level) effect size is Δ = 1.5 + 0.75 + 0.75 = 3.0, e.g. for those speaking English AND having high literacy AND watching the video

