Aim 2. Retention of HIV/AIDS and HIV testing knowledge at 3, 6, 9, and 12 months ** HA1**: 3-way interaction (mode*language*literacy level) ** HA2**: 2-way interaction (mode*language or literacy level) **HA3**: no interaction (difference by mode only) ** HA4**: no difference	**100** This **minimum** sample size by stratum will yield a power of 0.80, 0.97 and 0.99 for testing HA1, HA2, and HA3, versus HA4 (as the NULL)	**800** After adding 25% to account for loss-to-follow-up and 20% for heterogeneity among study sites, the **final sample** size is **1200** = 800*(1 + 25%)*(1 + 20%)	• Long-term within-person correlation is 0.4 or higher • The scores on the knowledge questionnaire in the pictorial brochure arm will degrade to the pre-information baseline level with an average drop of 2 points by 12 months. The score in the video information arm will degrade by an average drop of 1 point. So, compared to baseline, the difference (effect size) in long-term retention of information in the video arm as compared to the pictorial brochure arm is Δ = (3.5–1)-(2–2) = 2.5. • We will assume a similar effect size for 2- and 3-way interactions

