The generalized linear mixed-effect model will be structured as follows: *Y*^***^_*ij*_ *= α*_*j*_ *+ f(R*_*i*_*,LG*_*i*_*,LT*_*i*_*; β) +* μ_i_ *+ θX*_*i*_*,* where *j = 0,1* indicates pre- and post-information, *Y*^***^_*ij*_ is the outcome of subject *i*, R_i_ indicates the arm assignment, *α*_*j*_ is the intercept (*α*_*0*_ being the pre-information value for j = 0; and *α*_*1*_ the post-information value for j = 1), *β* is a vector that captures the main effects, and 2- and 3-way interactions among information delivery mode *(R),* language *(LG*), and literacy *(LT)*, *f* () is a linear predictor function, and *X*_*i*_ contains important or stratification covariates, with *θ*θ being their effects. For this unified approach, *Y*_*ij*_^***^ = *g*[E (*Y*_*ij*_)] where *g*() is an appropriate transformation of the outcome being analyzed. For example, for continuous outcomes, *g*() can be an identify link; for count or binary outcomes (as in the exploratory aims), *g*() can be a log or logit/probit transformation. We will assume that *u*_*i*_
*~ N(0, τ*^*2*^*)*, which is a random effect that captures the within-subject correlation of the repeated measurements. We will fit the models using the restricted maximum likelihood method, or generalized estimating equations (GEE) if non-identify links are used.

For Aim 2, we will first compare the baseline literacy scores at each of the follow-up visits to the baseline score (post-information delivery) using paired *t*-tests. If the retention of HIV/AIDS and HIV testing knowledge demonstrates a linear trend over time, we will fit a linear mixed-effect model to the combined data, in which independent variables will include time, information delivery mode, language and baseline health literacy level; their interactions; age, gender, etc. If the trend is not linear, we will consider fitting a broken-stick (piecewise linear) linear mixed-effect model. The parameters of interests are the coefficients of time, indicating follow-up assessments, and the interactions of time and study arm assignment, information delivery mode and language.

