If a linear assumption is supported by data, the linear predictor in the above model will be expressed as *α*_*0*_ *+ β*_*1*_*[time] + β*_*2*_*[time]*R*_*i*_*[mode]*, where *β*_*1*_ and *β*_*2*_ capture HIV/AIDS and HIV testing knowledge retention rate over time and the difference in the rate between two delivery modes. We will further evaluate the 2- and 3-way interactions *β*_*2*_*[time]*[language]*R*_*i*_
*[mode]* and *β*_*2*_*[time]*[health literacy level]*R*_*i*_*[mode]* and possibly (if data allow) 4-way interactions *β*_*2*_*[time]*[language]*[health literacy level]*R*_*i*_*[mode]*, to investigate the interaction of information delivery mode with language and health literacy and whether one delivery model works better in certain sub-groups. Our analysis by time will permit us to determine if and when HIV/AIDS and HIV testing knowledge degrades, and if and when knowledge reaches baseline pre-information levels (i.e., before an intervention), which would suggest a need for repeat delivery of this information at subsequent HIV testing encounters within 12 months. We also will determine if degradation varies by information delivery mode, language, and health literacy level. We recognized that there is no established minimum standard for what level of HIV/AIDS and HIV testing knowledge is necessary or desired; however, we believe that it should be at least greater than pre-information knowledge levels, and will plan the analyses accordingly.

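### The displayed Aim 2 model has no delivery-mode main effect and so contradicts the protocol's own variable list; fitted literally, it turns the expected post-information gap into a false difference in forgetting.

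*Protocol article*

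**What the plan says.** All of this is in the protocol article.

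- **Displayed predictor** (Primary aims analysis, Aim 2): α₀ + β₁[time] + β₂[time]·R[mode]. The coefficients β₁ and β₂ are said to "capture HIV/AIDS and HIV testing knowledge retention rate over time and the difference in the rate between two delivery modes".
- **Variable list** (same section, preceding paragraph): time, delivery mode, language and health literacy, their interactions, and covariates such as age and gender. Mode therefore appears in its own right.
- **Higher-order terms**: the language and literacy interactions are written with the same symbol β₂. The term combining time, mode, language and literacy is added only conditionally: "and possibly (if data allow) 4-way interactions".
- **Time zero**: Table 4 compares each follow-up visit with the post-information score in the ED.
- **Expected values**: Table 3 assumes gains of 3.5 points (video) and 2 points (brochure), then losses by 12 months of 1 and 2 points. It assumes the score "is a normal distribution with a standard deviation of ~ 3".
- **Within-person correlation**: the only random effect is a subject term with variance τ², "which is a random effect that captures the within-subject correlation of the repeated measurements". It is introduced for the pre/post model of Aim 1. Table 3 assumes 0.7 or higher in the short term and, for Aim 2, "Long-term within-person correlation is 0.4 or higher".

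**The concern.** Without a mode term, the displayed formula forces both arms through one value at time zero. Randomisation would justify that at the pre-information visit. It does not at the post-information visit, where the trial expects the arms already to differ. The time-by-mode coefficient is then the only place the starting gap can go, so a real Aim 1 effect would be reported a second time as better retention, in the model for a primary aim.

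Two smaller matters belong to the same model. HA1 of Aim 2 concerns mode, language and literacy jointly. In a slope model that is the four-way term with time, which the text leaves optional. And a single random intercept implies the same correlation at every lag, which sits uneasily with Table 3's two correlation values.

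**Working it through.** **Inputs.** SD 3, a starting gap of 3.5 − 2 = 1.5, and correlations of 0.7 and 0.4 (Table 3); visits t = 0, 3, 6, 9, 12 months (Table 4); 1:1 allocation; two-sided 5% level. The plan's Aim 2 sample reproduces: 800 × 1.25 × 1.20 = 1200. With 25% loss, 1200 × 0.75 = 900, or 450 per arm. The plan's minimum of 800 gives 400 per arm.

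**Step 1: what β₂ estimates when forgetting is equal.** With equal arms, β₂ is the generalised least squares slope of the arm difference D, forced through zero at t = 0: β₂ = t′V⁻¹D / t′V⁻¹t, with V = 9[(1−r)I + r11′]. Here Σt = 30 and Σt² = 270. Put c = r/(1+4r) and D = 1.5 at every visit. Then

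- 12-month β₂ = 12 × 1.5 × 30(1−5c) / (270 − 900c)
- SE = 12 × √[(2/n) × 9(1−r) / (270 − 900c)]

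At r = 0.4, c = 0.1538 and β₂ = 18 × 6.923/131.54 = 0.95. The true slope difference is zero throughout. With n = 450 per arm:

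| r | β₂ (points/year) | SE | P(declared non-zero) |
|---|---|---|---|
| 0.4 | 0.95 | 0.162 | 1.00 |
| 0.5 | 0.75 | 0.155 | 0.998 |
| 0.6 | 0.57 | 0.144 | 0.98 |
| 0.7 | 0.41 | 0.129 | 0.89 |

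With 400 per arm and the variance components estimated under the same formula, β₂ is 0.92 (r = 0.4, rejection about 100%) and 0.39 (r = 0.7, 81%). In 2000 simulated REML fits at r = 0.4, the mean β₂ was 0.915 and rejection 100%. With the mode main effect added, the mean was −0.001 and rejection 5.3%.

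**Step 2: under Table 3's own scenario.** Losses of 1 and 2 points make the true 12-month difference in decline 1.0. The bias adds to it: 1.95, 1.75, 1.57 and 1.41 for r = 0.4 to 0.7. With the main effect included, the estimate is 1.00.

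**Step 3: the random intercept, with the mode main effect included.** The slope then uses centred times x = (−6, −3, 0, 3, 6), with Σx² = 90. The true slope variance is proportional to x′Rx/90, where R is the correlation matrix. The random-intercept model uses 1 − (mean correlation) instead. With k the ratio of the two, type I error is 2[1 − Φ(1.96/√k)]. The decay shapes below are assumptions.

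| Correlation between visits | x′Rx/90 | 1 − mean | k | Type I error |
|---|---|---|---|---|
| Constant at 0.4 | 0.600 | 0.600 | 1.00 | 5% |
| Exponential, 0.7 near lag 0 to 0.4 at 12 months | 0.693 | 0.466 | 1.49 | 11% |
| Linear, 0.7 near lag 0 to 0.4 at 12 months | 0.690 | 0.450 | 1.53 | 11% |
| Linear, 0.7 at 3 months to 0.4 at 12 months | 0.720 | 0.400 | 1.80 | 14% |
| Exponential, 1 at lag 0 to 0.4 at 12 months | 0.787 | 0.352 | 2.24 | 19% |

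Simulation gave 15.3% and 20.4% for the last two rows.

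**The case against.** The strongest defence is that the formula is shorthand. It also leaves out language, literacy, covariates and the subject effect, all of which the text provides for, and it reuses β₂ for every interaction. An analyst who follows the variable list obtains an unbiased slope contrast. This stands as far as it goes: a reader might infer that the protocol has settled on a biased primary analysis, and the documents do not support that. They do contain two incompatible statements of one primary model.

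It can also be said that α₀ is defined, in the Aim 1 model, as the pre-information value, where a common intercept would be sound. Table 4 rules this out for Aim 2. And Table 3's effect of 2.5 is measured from pre-information, so it includes the Aim 1 gap (1.5 + 1.0). That is a different target from β₂, which the text defines as a difference in rate; for that, 1.0 is the right comparison.

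A reader might further infer that the standard errors are too small in general, or because the mode term is missing. Neither follows. With constant correlation the standard errors are right. Table 3's correlations are lower bounds, its 0.7 is the short-term value used for Aim 1, and the random intercept reaches Aim 2 only through a reference back to the earlier model.

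Lastly, choosing between straight-line and broken-stick decline from the data ("If the trend is not linear, we will consider fitting a broken-stick (piecewise linear) linear mixed-effect model") might look like post hoc selection. Table 4 names both shapes in advance, and the decision rule is detail that a protocol article may leave out.

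**Conclusion.** The point holds as a contradiction to reconcile. The displayed Aim 2 formula disagrees with the variable list beside it and is wrong for the meaning given to β₂. Fitted literally, it yields a false slope difference of about 0.4 to 0.95 points per year, declared non-zero with probability about 0.8 to 1.0, and inflates a true difference of 1.0 to about 1.4 to 1.95. These figures rest on Table 3's 1.5-point gap and SD of 3, constant correlation of 0.4 to 0.7, and 400 to 450 participants per arm. A 0.5-point gap at 400 per arm still gives false rejection of 17 to 45% across the correlation patterns examined, including decaying ones. With no gap and constant correlation the rate is 5%.

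The covariance point is conditional: type I error of about 11 to 19% if correlation falls over follow-up in one of the assumed shapes, and the nominal 5% if it does not. Leaving the four-way term optional is inconsistent with its status as HA1 of a primary aim, for which Table 3 claims power of 0.80.

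**What to change.** 1. Make the displayed predictor agree with the variable list. Add the mode main effect and every lower-order term of each interaction, and give each term its own coefficient.
2. Keep the time-by-mode coefficient as the rate-of-decline contrast. Replacing it with the arm difference at 12 months adjusted for the pre-information score would not cure the problem: under equal forgetting that contrast equals the full 1.5-point gap, and it answers a question about level, not rate.
3. Fit the time-by-mode-by-language-by-literacy term as a fixed contrast and drop the condition on the data.
4. State the Aim 2 covariance: a random slope, a serial or unstructured covariance, or robust standard errors.

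If site is added as a fixed effect, note that the planned recruitment nests sites within language (Study sites and recruitment feasibility), so four site effects would be confounded with the language main effect.

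The cost is wording and a few more model parameters, with no change to data collection or sample size.

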### Study analysis (begins at end of recruitment month 43)

#### Enrollment summary and comparison of participants at baseline

We will report on participant enrollment and summarize the reasons for accepting or declining enrollment or drop-out from the study using the Consolidated Standards of Reporting Trials (CONSORT) approach [62]. We will summarize the demographic characteristics, HIV testing history, and health literacy level (measured by the SAHL-S&E [22] and brief instruments) using conventional statistics, such as means/standard deviations, medians/ranges, or counts/frequencies with corresponding 95% confidence intervals (CIs), as appropriate. For Latino participants, we will summarize nativity and US acculturation (measured by the SASH [63, 64]) in a similar manner. We will summarize these baseline characteristics for all participants and as stratified by informational delivery mode (pictorial brochure or video), language preference (English or Spanish), and health literacy level (lower or higher). Next, we will compare the baseline characteristics of study participants between the study arms using Pearson’s Χ^2^ or Fisher’s exact test for categorical variables and Student’s t-test for normally distributed or Wilcoxon’s rank-sum test for non-normally distributed continuous variables to assess the success of the randomization procedure. Any chance imbalances between the two arms will be documented and investigated, and will be adjusted for by including the imbalanced covariate as an independent variable in our subsequent regression analyses, or through a weighted analysis using a propensity score (propensity to be enrolled in the study with weights equal to the inverse of the propensity score) [65]. A two-tailed, *α = 0.05* significance level will be used for all analyses.

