#### Primary aims analysis

For Aim 1, we expect that HIV/AIDS and HIV testing knowledge scores can be reasonably approximated by a normal distribution (Table 4). We will compare differences in pre- vs. post- changes in scores between information delivery modes by paired t-tests. If the data are not normally distributed, we will use signed-rank tests. All tests will be executed on an intention-to-treat basis (non-adherence to assigned information delivery mode likely is minimal). Comparisons will first be made for each stratum. MANOVA/ANCOVA will be used for combined samples where language and literacy level are used as stratifying (main) factors. To further account for baseline covariates (e.g., demographic characteristics), a generalized linear mixed-effect model will be fit to the data. The parameters of interest are the coefficients of the dummy variable indicator of study arm assignment and its interactions with language and health literacy level.

**Table 4 Tab4:** Analyses of primary aims

Primary aims	Measurements	Analytic methods
Aim 1. Short-term improvement in HIV/AIDS and HIV testing knowledge **HA1**: 3-way interaction (mode*language*literacy level) **HA2**: 2-way interaction (mode*language or literacy level) **HA3**: no interaction (difference by mode only) **HA4**: no difference	HIV/AIDS and HIV testing knowledge questionnaire at baseline in ED at time of HIV testing, post- vs. pre-information delivery	• Paired t-tests • Signed-rank tests • MANOVA/ANCOVA • Generalized linear mixed-effects regression
Aim 2. Retention of HIV/AIDS and HIV testing knowledge at 3, 6, 9, and 12 months **HA1**: 3-way interaction (mode*language*literacy level) **HA2**: 2-way interaction (mode*language or literacy level) **HA3**: no interaction (difference by mode only) **HA4**: no difference	HIV/AIDS and HIV testing knowledge questionnaire at 3, 6, 9, and 12 months vs. baseline (post-information delivery)	• Paired t-test for each follow-up vs. baseline • Linear mixed-effects regression (assuming constant degradation over time) • Broken-stick linear mixed-effects regression (for non-constant degradation over time)

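### Aim 2 promises to show when knowledge falls back to its pre-information level, but no specified Aim 2 contrast compares follow-up with the pre-information score

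*Protocol article*

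**What the plan says.** All places are in the protocol article.

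- **The question.** The last paragraph on Aim 2 under Primary aims analysis says the analysis by time will show "if and when knowledge reaches baseline pre-information levels (i.e., before an intervention), which would suggest a need for repeat delivery of this information". It accepts that no minimum standard of knowledge exists, but holds that "it should be at least greater than pre-information knowledge levels, and will plan the analyses accordingly".
- **The sample size.** The Aim 2 row of Table 3 measures retention from the same level. Brochure gains 2 points and loses 2, video gains 3.5 and loses 1, and the effect is (3.5 − 1) − (2 − 2) = 2.5.
- **The comparison.** The Aim 2 row of Table 4 gives the measurement as "HIV/AIDS and HIV testing knowledge questionnaire at 3, 6, 9, and 12 months vs. baseline (post-information delivery"). The text repeats that reference for the paired t-tests, which compare scores "at each of the follow-up visits to the baseline score (post-information delivery").
- **The models.** Linear or broken-stick mixed models follow the paired tests. Their stated parameters of interest are the coefficients of time and the interactions of time with mode and the strata. The Aim 2 linear predictor has one intercept, α0. The Aim 1 model defines α0 as the pre-information value and gives the post-information value its own symbol, α1.

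**The concern.** The word baseline has two meanings within one aim. For the practical question and the effect size it is the score before the video or brochure. For the specified comparison it is the score after it. A fall from the post-information score shows that some of the gain has gone. It does not show whether any gain is left, and that is what the plan says would indicate repeat delivery.

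The slopes do not supply the answer either, because they are rates of loss. A group that gains 3.5 and loses 2 ends 1.5 points above where it started; a group that gains 2 and loses 2 ends at zero. Both have the same slope.

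At stake is a headline output. The Abstract and the section on the current research both say the results will tell EDs when, how and for whom information should be given to patients re-tested within a year.

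**Working it through.** **Inputs**
- Score SD: Table 3 assumes the score "is a normal distribution with a standard deviation of ~ 3". I take 3 at every time point.
- Correlation: "Long-term within-person correlation is 0.4 or higher" (Table 3, Aim 2). I use 0.4 for follow-up against either the pre- or the post-information score, since the table does not distinguish them.
- Gains and 12-month drops: as in Table 3.
- Size: 150 per language-by-literacy-by-mode cell, with 25% attrition (Sample size considerations). 75% of 150 is 112.5, taken as 112. Per arm, 75% of 600 is 450.
- Test level: two-tailed 0.05, which the plan says "significance level will be used for all analyses".

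**Step 1. The plan's own figures.** Δ = (3.5 − 1) − (2 − 2) = 2.5. For N, the minimum of 800 plus 25% is 1000, and that plus 20% is 1200. Both reproduce. From the post-information score, the same assumptions give a between-arm difference of (−1) − (−2) = 1.0, so the two references are not interchangeable.

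**Step 2. Precision of a paired change.**
SD of change is 3 × √(2 × (1 − 0.4)), which gives 3.29.
SE is SD divided by √n: with n of 112 this gives 0.311 per cell, and with n of 450 it gives 0.155 per arm.

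**Step 3. Probability of a significant paired t-test at 12 months (noncentral t).**

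| Group | True change from post | Per cell, n = 112 | Per arm, n = 450 | True distance above pre |
|---|---|---|---|---|
| Video | −1 | 0.89 | >0.99 | 2.5 |
| Brochure | −2 | >0.99 | >0.99 | 0 |

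Hand check for video in one cell: 1 divided by 0.311 is 3.22, less the critical value of about 1.98, leaves 1.24, and Φ(1.24) is 0.89.

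Sensitivity for video: 0.85 with Table 3's minimum of 100 per stratum, and 0.995 with n = 112 and correlation 0.7. The conclusion is the same in each case.

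**Step 4. The same groups against the pre-information score, n = 112.** Video: 2.5 divided by 0.311 is 8.0 standard errors, so significance is near certain. Brochure: true difference 0, so the two-sided test rejects in 5%, of which 2.5% has the lower bound above zero. This contrast separates the groups.

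**Step 5. The models.** Distance above the pre-information level equals gain minus loss. A slope estimates only the loss. Recovering the distance needs both the pre- and the post-information level, and the written Aim 2 predictor has one intercept. If α0 keeps its Aim 1 definition, it is the pre-information value and conflicts with the post-information reference in Table 4. If it means the post-information value, the pre-information level does not appear.

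**The case against.** The strongest reply has four parts.

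1. **The paired test is not the only Aim 2 analysis.** A reader might infer that it is. The documents do not support that: linear and broken-stick mixed models are also specified, and the paired tests come first as a preliminary. What remains is that the parameters named for those models are slopes and interactions, not the distance from the pre-information score.

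2. **The trial can answer the question.** A reader might infer that return to baseline is undecidable. That is also unsupported. Table 2 shows the knowledge questionnaire given before and after the information and at every follow-up. Fitted means could be set beside the pre-information mean, and the estimated drops could be read against the Aim 1 gains. The gap lies in the specified contrasts, not in the data.

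3. **The intention is stated, and detail may sit in an analysis plan not shown.** This holds for a margin or a confidence-bound rule, whose absence is no error here. It does not cover the reference: the article fixes it as post-information twice, in Table 4 and in the text, against its own stated intention.

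4. **Return to baseline is an interpretive remark, not a hypothesis.** HA1 to HA4 do concern variation by mode, language and literacy, and a post-information reference is a sound way to measure degradation. Even so, the article says the analysis will permit this determination and rests a practice conclusion on it.

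A reader might also infer that the plan would declare knowledge returned from a non-significant test. Nothing in the article says so.

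**Conclusion.** The point holds in this form: none of the specified Aim 2 contrasts compares follow-up with the pre-information score, although the article's practical question and its Aim 2 effect size both use that score. On Table 3's assumptions, the written paired test is significant with probability about 0.89 per cell for a group 2.5 points above the pre-information level and >0.99 for a group at it. Per arm, both exceed 0.99.

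These figures rest on SD 3, the lower limit of the assumed correlation, and the attrition the plan itself calls a likely worst case. Higher correlation or better follow-up brings the video figure closer to 1, so the two groups become harder still to tell apart by significance.

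This should be corrected, but it does not undermine the design or the between-arm hypotheses.

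**What to change.** - Keep the post-information comparison in Table 4 and the text as the measure of degradation.
- Add the mean of follow-up minus pre-information score with a 95% CI at 3, 6, 9 and 12 months, by mode and by language-by-literacy cell. Estimate it from a mixed model that includes the pre-information measurement and visit.
- Conclude that knowledge is still above the pre-information level when the lower bound exceeds 0, which is the plan's own threshold.
- State that a non-significant difference will not be read as return to baseline. As a caution: per cell the 95% CI half-width is about 0.62 point, and a true residual gain of 0.5 would be non-significant in about 64% of cells (power 0.36 at correlation 0.4).
- Use distinct terms for the pre- and post-information scores, and give α0 one meaning, across Table 3, Table 4 and the Aim 2 model text.

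If the sponsor also wants to declare that knowledge has returned, it must set a margin in advance. That choice is the sponsor's, and its absence is not part of the error.

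**Cost:** analysis wording only, with no new data. Some cells will be reported as undetermined.
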